# Prostate Cancer Survivorship Essentials for men with prostate cancer on androgen deprivation therapy: protocol for a randomised controlled trial of a tele-based nurse-led survivorship care intervention (PCEssentials Hormone Therapy Study)

**DOI:** 10.1136/bmjopen-2024-084412

**Published:** 2024-03-23

**Keywords:** prostatic neoplasms, randomized controlled trial, health education, nursing Care, quality of life

## Abstract

**Introduction:**

Androgen deprivation therapy (ADT) is commonly used to treat men with locally advanced or metastatic prostate cancer. Men receiving ADT experience numerous side effects and frequently report unmet supportive care needs. An essential part of quality cancer care is survivorship care. To date, an optimal effective approach to survivorship care for men with prostate cancer on ADT has not been described. This protocol describes a randomised trial of tele-based nurse-led survivorship that addresses this knowledge gap: (1) determine the effectiveness of a nurse-led survivorship care intervention (PCEssentials), relative to usual care, for improving health-related quality of life (HR-QoL) in men with prostate cancer undergoing ADT and (2) evaluate PCEssentials implementation strategies and outcomes, including cost-effectiveness, compared with usual care.

**Methods and analysis:**

This is an effectiveness-implementation hybrid (type 1) trial with participants randomised to one of two arms: (1) minimally enhanced usual care and (2) nurse-led prostate cancer survivorship essentials (PCEssentials) delivered over four tele-based sessions, with a booster session 5 months after session 1. Eligible participants are Australian men with prostate cancer commencing ADT and expected to be on ADT for a minimum of 12 months. Participants are followed up at 3, 6 and 12 months postrecruitment. Primary outcomes are HR-QoL and self-efficacy. Secondary outcomes are psychological distress, insomnia, fatigue and physical activity. A concurrent process evaluation with participants and study stakeholders will be undertaken to determine effectiveness of delivery of PCEssentials.

**Ethics and dissemination:**

Ethics approval was obtained from the Metro South Health HREC (HREC/2021/QMS/79429). All participants are required to provide written informed consent. Outcomes of this trial will be published in peer-reviewed journals. The findings will be presented at conferences and meetings, local hospital departments, participating organisations/clinical services, and university seminars, and communicated at community and consumer-led forums.

**Trial registration number:**

ACTRN12622000025730.

STRENGTHS AND LIMITATIONS OF THIS STUDYThe effectiveness-implementation design allows for a concurrent process evaluation which will provide immediate implementation data.A cost–utility analysis will provide important economic evaluation data.Tele-based interventions are highly acceptable to men with prostate cancer and applicable to geographically dispersed and vulnerable populations.The pragmatic decision to exclude non-English speaking patients from the trial may influence the generalisability of study findings to patients from linguistically diverse backgrounds.

## Introduction

Prostate cancer (PCa) is the most common cancer diagnosed in Australia.^1^ While men are living longer following diagnosis, longitudinal research has characterised a subgroup of 35%–40% of men who experience long-term decrements in health-related quality of life (HR-QoL).^2^ In particular, men who are on androgen deprivation therapy (ADT) experience consistently poorer physical and mental HR-QoL over the long term.^2–6^

While ADT is effective in treating PCa and increasing survival, it is associated with multiple, often debilitating side effects, which manifest as changes in physical, cognitive, social and sexual functioning.^3 7–9^ Iatrogenic effects may include mood disturbances, increased fat mass, body feminisation, cognitive decline, functional impairment, frailty, fatigue and sexual dysfunction.^3 4 6–10^ ADT also increases the risk of developing new comorbidities, including cardiovascular conditions, diabetes, sarcopenia and osteoporosis.^11^ Compared with men receiving other treatments, those undergoing ADT report poorer HR-QoL and higher levels of psychological distress, including depression, anxiety, relationship changes, cognitive and affective symptoms, and sleep disturbances.^3 4 6–9 12^ The prevalence of psychological distress in PCa survivors is reported to be between 11% and 27%,^13^ and regardless of other treatments, receiving ADT is predictive of higher distress.^12^ Further, men undergoing ADT have an increased risk of suicide compared with those who do not, particularly in older men and in the first 6 months postdiagnosis.^14^ Unmet supportive care needs are highly prevalent in these men, with unmet physical, psychological, sexual, existential and informational^12 15^ needs that persist at 15 years postdiagnosis.^16^ Over one-third (37%) of men with PCa will report at least one long-term unmet supportive care need particularly at the start of treatment when side effects are new or unknown and HR-QoL is first impacted.^16^ This is of particular concern for men receiving ADT who report feeling unprepared to manage substantial treatment side effects that impact on quality of life.^17^ Further, despite routine clinical follow-up, men receiving ADT rarely receive tailored person-centred interventions in a timely manner, adversely impacting HR-QoL with poor management of side effects and self-efficacy.^12 15^ Men treated with ADT are a vulnerable high-need patient group for whom evidence-based survivorship care is crucial.

### Preliminary research on survivorship care for men with PCa

Previous PCa survivorship guidelines published by the American Cancer Society a decade ago^18^ were limited by an over reliance on expert opinion and lack of a robust evidence base.^19^ Existing survivorship guidelines have also been limited by lack of consumer involvement.^20 21^ Our group has contextualised survivorship care for PCa^20 22 23^ and produced a contemporary survivorship care framework for men with PCa. The resulting survivorship essentials framework (figure 1) proposes holistic survivorship care for men with PCa and was developed by a uniquely inclusive expert clinical and community group.^23^ The framework has been widely endorsed by key PCa and urological groups in Australia and New Zealand. Based on our survivorship framework, we have developed a new model of care, prostate cancer survivorship essentials (PCEssentials), which integrates evidence-based strategies to improve men’s quality of life outcomes after ADT in a men-centred approach, where personal agency intersects with all aspects of care.

**Figure 1 F1:**
[figure not shown]
Prostate Cancer Survivorship Essentials Framework.^23^

We propose an Australian effectiveness-implementation hybrid (type 1) randomised trial^24^ of tele-based nurse-led survivorship care with 236 PCa survivors undergoing ADT. This is the first such study internationally to address this problem. The proposed study will have two arms: (1) minimally enhanced usual care and (2) nurse-led prostate cancer survivorship essentials (PCEssentials) delivered over four tele-based sessions, with a subsequent booster session 5 months after the first session. In accordance with a type 1 hybrid trial, a concurrent process evaluation, guided by the conceptual framework for implementation outcomes,^25^ will be undertaken to determine effectiveness of the PCEssentials intervention delivery, and the potential for implementation of the intervention at scale.

### Aims

Aim 1: Determine the effectiveness of a nurse-led survivorship care intervention (PCEssentials), relative to usual care, for improving HR-QoL in men with PCa undergoing ADT.

Aim 2: Evaluate PCEssentials implementation strategies and outcomes, including cost-effectiveness of PCEssentials, with respect to usual care, as well as acceptability, adoption, appropriateness, feasibility, fidelity, penetration and sustainability.

### Primary hypothesis

We hypothesise that PCEssentials will be more cost-effective than usual care. Furthermore, relative to men receiving usual care at 3, 6 and 12 months after recruitment, men who receive PCEssentials will have: (1) higher HR-QoL, (2) increased self-efficacy, (3) less psychological distress and (4) improved sleep and lower fatigue.

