### Research outcomes and measurement tools

Previously validated and reliable patient-reported outcome assessments are administered by mail to men at four time points: baseline/recruitment (T1), 3 months (T2), 6 months (T3) and 12 months (T4) after recruitment. Primary outcomes are HR-QoL and self-efficacy. Secondary outcomes include global psychological distress, insomnia, fatigue and life satisfaction. Demographic moderators/disease variables (eg, cancer grade, stage, time since diagnosis, time since treatment) and a health service use diary are self-reported. Assessments are self-reports with pen and paper.

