#### Secondary outcomes

##### Psychological distress

The Generalised Anxiety Disorder (GAD-7) scale^47^ and the depression subscale of the Patient Health Questionnaire (PHQ-9)^48^ will measure psychological distress. The seven-item GAD-7 scale screens for, and assesses the severity of, GAD in clinical practice and research. The nine-item PHQ-9 scale screens for, and assesses the severity of, depression and includes a specific item on suicidal ideation.

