#### Intervention effectiveness

The study is a two-arm randomised controlled trial with repeated assessments across time and with continuous primary outcome variables. Recruitment bias will be assessed by comparing sociodemographic and clinical variables for consenters with non-consenters using t-tests (or Mann-Whitney U tests) for continuous variables and χ^2^ tests for categorical variables. Possible differential attrition will be assessed by comparing baseline characteristics of drop-outs and continuing participants using t-tests (or Mann-Whitney U tests if appropriate) for continuous variables and χ^2^ tests for categorical variables. Intention-to-treat analyses will be conducted. Between-group mean differences in change from baseline outcome scores at 3, 6 and 12 months will be analysed by fitting mixed effects regression models. Intervention (intervention/usual care) will be included as the main effect. Indicators for participants will be included as a random effect to account for the non-independence of repeated observations from the same individual. Sensitivity analysis will assess the effects of attrition. Mixed effects models with maximum likelihood estimation minimise bias that may arise from ignoring missing observations, and use all available data, thereby maximising statistical power to detect effects. The mean and 95% CI will be calculated for satisfaction with the intervention. Missing data will be examined for patterns of missingness and addressed with the appropriate multiple imputation methods, if required. The investigator team includes a dedicated biostatistician who will undertake analyses.

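### The primary hypothesis takes in outcomes the protocol elsewhere calls secondary, and the sample size rests on one of them, so the result that decides the hypothesis is not fixed

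*Protocol article*

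**What the plan says.** The section headed Primary hypothesis opens with a claim of better cost-effectiveness. It then states directional claims "relative to men receiving usual care at 3, 6 and 12 months after recruitment": items 1 and 2 are better HR-QoL and self-efficacy, and the list continues "3) less psychological distress and (4) improved sleep and lower fatigue". Nothing in that section ranks the items or marks any of them as secondary.

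The section Research outcomes and measurement tools says "Primary outcomes are HR-QoL and self-efficacy" and "Secondary outcomes include global psychological distress, insomnia, fatigue and life satisfaction". The Abstract says "Secondary outcomes are psychological distress, insomnia, fatigue and physical activity". These two lists differ in their last item but agree that distress, insomnia and fatigue are secondary. The instrument descriptions follow the same split. Under the secondary heading they place the GAD-7 "and the depression subscale of the Patient Health Questionnaire (PHQ-9") for distress, the Insomnia Severity Index for sleep and the MFSI-SF for fatigue. Aim 1 names HR-QoL alone.

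Statistical considerations and data analysis takes a third position. It calls psychological distress at 12 months the primary outcome and bases the sample size on it: d = 0.40, 80% power, alpha 0.05, 99 per group, 236 in total after 15% attrition.

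Intervention effectiveness gives one analysis for all outcomes: "Between-group mean differences in change from baseline outcome scores at 3, 6 and 12 months will be analysed by fitting mixed effects regression models". It does not say which outcome and visit decide the primary hypothesis.

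**The concern.** A primary hypothesis should tell the reader, before the data are seen, which result will settle the trial's main claim. Here three sections give three answers:

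- the hypothesis: HR-QoL, self-efficacy, distress, sleep and fatigue (plus cost-effectiveness), at three visits;
- the outcome list: HR-QoL and self-efficacy;
- the sample-size paragraph: distress at 12 months.

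A statistical analysis plan cannot agree with all three. If it treats distress, sleep and fatigue as secondary, it departs from the hypothesis. If it follows the hypothesis, it departs from the outcome list. Either way, the sample-size paragraph has to be explained.

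At stake is the reading of a mixed result. Suppose HR-QoL and self-efficacy show nothing and insomnia at 3 months is nominally significant. The outcome list says the primary outcomes failed. The hypothesis section lets an author write that the primary hypothesis was partly supported. In the opposite case, with HR-QoL improved and fatigue not, a strict reader could say that the hypothesis failed.

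**Working it through.** **1. The plan's own figure.** Inputs, from Statistical considerations and data analysis: d = 0.40, power 80%, alpha 0.05. Two-sided normal approximation: n = 2 × (1.960 + 0.842)² / 0.40² = 98.1, so 99 per group; the exact t-test solution is 99.08. One-sided alpha would give 78. The stated 99 therefore reproduces and implies two-sided 0.05. For attrition, 99 / 0.85 = 116.5 and 100 / 0.85 = 117.6; the stated 118 per group (236 in total) agrees with the second. No stated figure is wrong. The difficulty is the outcome to which the figure is attached.

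**2. The sections side by side.**

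| Outcome | Primary hypothesis | Outcome list and Abstract | Sample-size paragraph |
|---|---|---|---|
| HR-QoL | included, 3/6/12 months | primary | not named |
| Self-efficacy | included, 3/6/12 months | primary | not named |
| Distress | included, 3/6/12 months | secondary | primary, 12 months |
| Sleep | included, 3/6/12 months | secondary | not named |
| Fatigue | included, 3/6/12 months | secondary | not named |

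No outcome has the same status in all three columns. Only the sample-size paragraph singles out a visit.

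**3. If any one secondary result counted as support.** Assumed count: GAD-7, PHQ-9, Insomnia Severity Index and MFSI-SF total, at three visits, 4 × 3 = 12 tests. Each is two-sided at 0.05, and only results favouring the intervention count, because the hypothesis is directional; each test then has a 0.025 chance of a false positive. With no true effect:

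- Independent tests: 1 − 0.975¹² = 0.262.
- Equal correlation ρ: 1 − ∫ φ(u) Φ[(1.96 − √ρ·u)/√(1 − ρ)]¹² du, which gives 0.160 at ρ = 0.5 and 0.093 at ρ = 0.8.

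Letting correlation differ between scales and between visits gives 20% (0.3 between scales, 0.5 between visits), 17% (0.5, 0.6) and 13% (0.7, 0.7), all inside that range.

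If distress is taken as primary, as the sample-size paragraph has it, two secondary scales by three visits leave six tests. Independence gives 1 − 0.975⁶ = 0.141; the same formula with exponent 6 gives 0.104 at ρ = 0.5 and 0.069 at ρ = 0.8.

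**4. If every component had to succeed.** Assumed count: six scores at 12 months (one HR-QoL score, self-efficacy, GAD-7, PHQ-9, Insomnia Severity Index, MFSI-SF total), each with a true effect giving 80% power. The cost-effectiveness claim is left out.

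- Independent scores: 0.80⁶ = 0.262.
- Equal correlation ρ: ∫ φ(u) Φ[(0.842 + √ρ·u)/√(1 − ρ)]⁶ du, which gives 0.478 at ρ = 0.5 and 0.616 at ρ = 0.8.

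Requiring success at all three visits (18 tests) lowers this to 29% at ρ = 0.5 (2% at 0, 51% at 0.8).

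**The case against.** The strongest reply has four parts.

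*The protocol does have a hierarchy.* This is correct. The Abstract and the outcomes section separate primary from secondary outcomes, and the instrument headings keep to that. The Primary hypothesis section ignores the split, and the sample-size paragraph contradicts it.

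*The hypothesis joins its items with a conjunction.* Also correct. A reader might infer that one chance result on a secondary scale would confirm the primary hypothesis. The document does not support that: no section says one component is enough, and read literally all are required. But no section states an all-of rule either, and the sample size is not built for one. Neither reading is fixed.

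*Multiplicity rules for secondary outcomes belong in the analysis plan.* This stands. The absence of gatekeeping, an alpha split or an exploratory label from a condensed article is not a finding, and none is claimed here. The point concerns what the printed sections state and how they disagree.

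*The error rates are illustrations.* Agreed. A reader might quote the two-sided any-of-12 rate, 32% at a correlation of 0.5, but that counts results favouring usual care, which cannot support a directional claim. Nor does any rate here breach a familywise level that the protocol promises: its 0.05 is attached to the single powered outcome.

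**Conclusion.** The point holds as an inconsistency in the printed text. The Primary hypothesis section includes distress, sleep and fatigue at three visits, the outcome lists class them as secondary, and the sample-size paragraph makes distress at 12 months primary. The result that decides the primary hypothesis is therefore not fixed.

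The consequence depends on a success rule that the document leaves open. Under an any-of reading of the 12 secondary tests, the chance of a false favourable result is about 16% (9% to 26%). Under an all-of reading of six scores at 12 months, joint power is about 48% (26% to 62%) in place of the stated 80%. The scale counts, the equal correlations from 0 to 0.8, and 80% power for each score are assumptions. The inconsistency itself rests on none of them. It should be corrected, and the sample-size arithmetic is sound as it stands.

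**What to change.** Reconcile three sections in one edit, before analysis:

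1. **Primary hypothesis:** limit it to the designated primary outcome(s) and one time point.
2. **Research outcomes and measurement tools:** make the primary designation match, and settle whether distress is primary or secondary. The same designation should appear in the Abstract.
3. **Statistical considerations and data analysis:** make the sample-size statement refer to that same outcome and time point. Moving distress to the secondary hypotheses without this step would leave the sample-size paragraph contradicting the revised text.

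State the remaining outcomes and visits as secondary hypotheses that cannot by themselves support the primary claim. Any formal multiplicity procedure for them can stay in the analysis plan.

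The cost is wording only, with no extra data; if the sample-size outcome changes, its effect-size justification must be restated for the new outcome. The downside is that an isolated secondary or early-visit result can no longer be claimed as support for the primary hypothesis.

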## Methods and analysis

### Study design

A type 1 effectiveness-implementation hybrid randomised trial^24^ of a nurse-led survivorship care intervention (PCEssentials), relative to usual care, for improving HR-QoL in men with PCa undergoing ADT. A concurrent process evaluation will determine the effectiveness of intervention delivery, and the potential for implementation at scale. The study design has been guided by the Consolidated Standards of Reporting Trials (CONSORT) criteria.^26^

There are four key study time points:

T1—baseline: prior to randomisation.T2—3 months postrecruitment.T3—6 months postrecruitment.T4—12 months postrecruitment.

This study will be undertaken in accordance with the National Statement on Ethical Conduct in Human Research (2007—updated 2018)^27^ and the Australian Code for the Responsible Conduct of Research (2018).^28^ The study commenced in January 2022 on receiving ethics approval, with a planned end date of August 2026.

### Research population

There are two research populations for this study:

Patient participants (n=236): Australian men (aged 18 years or over) diagnosed with PCa commencing, or within 3 months of having commenced, ADT.Process evaluation participants (n=148): Study stakeholders (n=30) who are directly involved in study delivery and/or translation into clinical practice, including participating service managers, recruiting clinicians, nurses delivering the intervention, health professionals and patient participants in the intervention group (n=118). While all participants in the intervention group will complete programme acceptability assessments at two study time points (T1 and T3), approximately 20 of these patient participants will be purposively selected/invited to take part in a semistructured interview (T3) to explore their experiences of the intervention. Purposive sampling will ensure a patient subgroup with maximum diversity (eg, based on age, background, location, partnered or unpartnered). We anticipate reaching data saturation for the process evaluation with this number of participants.

### Inclusion criteria

Men recruited to the study will (1) have been diagnosed with PCa and be commencing, or within 3 months of having commenced ADT, and expected (based on clinical information) to be on ADT for a minimum continuous period of 12 months; (2) are able to read and speak English; (3) are able to give written informed consent; (4) have no history of head injury, dementia or psychiatric illness; (5) have no other concurrent cancer and (6) have mobile and/or landline phone access.

### Exclusion criteria

Men with castrate resistant and confirmed metastatic disease are excluded on the basis of having progressive and incurable disease that may rapidly progress and the study doesn’t meet their needs.

### Research project setting/location

There are multiple recruitment settings through clinicians in major treatment centres across Australia and by patient self-referral. Study information for patient self-referral is disseminated through investigator networks.

### Research project procedures

#### Intervention

Following referral (clinician or self) to the study team, research staff screen potential participants for eligibility and conduct an informed consent process (figure 2). Once eligibility is confirmed, and written informed consent received, participants receive the baseline assessments (T1) via mail. On return of T1 assessments, the study team randomises participants into the intervention or minimally enhanced usual care (‘usual care’) group.

**Figure 2 F2:**
[figure not shown]
Study diagram.

Men randomised to the intervention group commence the PCEssentials intervention, a five-session psychoeducation programme delivered by trained PCa specialist nurses via mobile and/or landline telephone. This includes four sessions over 3 months and a booster session at 5 months after the first session. Men in the intervention group are also be offered a home-based exercise programme and encouraged to seek at least one planning session with an accredited exercise physiologist (AEP).

Men in the usual care group receive their standard management, minimally enhanced with a package of evidence-based resources.

Men in both groups will continue to attend their standard PCa related care and complete study assessments at 3, 6 and 12 months postrecruitment.

